### Procedure

At the Screening Visit, eligible participants provide written, informed consent for all study procedures. Each patient undergoes screening evaluations that include a full psychiatric consultation to confirm a diagnosis of MDD using the Mini International Neuropsychiatric Interview (MINI) [8]. Previous medication history (type, dose, and duration) is collected using the Antidepressant Treatment History Form (ATHF) [9]. A detailed medical history and listing of concomitant treatments, if any, are recorded. A reproductive/menstrual history is obtained from female patients. Patients undergo medical work-up that includes physical examination, height and body weight measurements, clinical laboratory assays, and 12-lead electrocardiography (if indicated). Social background is collected using standardized reporting forms for demographic characteristics, handedness, ethnicity, education (expressed as years of formal schooling), marital status, occupational status, job classification, and household income. Participants are screened for contraindications to magnetic resonance imaging (MRI).

Figure 1 shows an overview of the protocol. At the Baseline Visit (Visit 1, Week 0), extensive clinical assessments are conducted, and blood and urine samples are obtained for molecular analysis. Participants also undergo the first of 3 sessions of structural and functional neuroimaging and electroencephalography (EEG), as described below. All patients start treatment with escitalopram and receive standardized clinical management based on the CANMAT clinical guidelines [10].

**Fig. 1 Fig1:**
[figure not shown]
CAN-BIND-1 Clinical Protocol

Neuroimaging/EEG, molecular and clinical assessments are conducted again at Weeks 2 and 8. Additional blood samples are collected at Week 4 for pharmacogenetic analysis, and at Weeks 2, 10, and 16 for medication levels. Blood chemistry screening, urinalysis, and body weight measurements are repeated at Week 16. At the conclusion of the study, patients are discharged into standard clinical care by a family physician and/or regular psychiatrist. Patients can also elect to enrol in a long-term naturalistic follow-up study that includes wellness monitoring using electronic mental health (e-Mental Health) tools.

Healthy comparison participants attend 5 study visits: Screening, Baseline, Week 2, Week 8, and Week 16. They complete the same assessments as patients but do not receive any treatment.

### Treatments

In Phase 1, patients receive flexibly dosed escitalopram (10–20 mg/d) for 8 weeks. Patients are started at 10 mg/d and increased to 20 mg/d at Week 2 if they do not achieve ≥20 % reduction in MADRS score from baseline, and at Week 4 for those who do not achieve ≥50 % reduction in MADRS.

In Phase 2, patients who achieve ≥50 % reduction in baseline MADRS score at Week 8 are considered “responders” and continue on their effective dose of escitalopram for a further 8 weeks. Patients who do not achieve ≥50 % reduction in MADRS are considered “non-responders” and receive flexibly dosed aripiprazole (2–10 mg/d), added to escitalopram, for a further 8 weeks. Dose increases of aripiprazole are recommended if patients do not achieve ≥50 % reduction in MADRS after 2 or 4 weeks.

This standardized algorithm reflects usual clinical practice, is consistent with evidence-based treatment guidelines [11–13], and promotes consistency across all sites. Doses can be decreased at the discretion of the treating psychiatrist if patients do not tolerate higher doses. Treatment is open-label, and no randomization procedures are used. Medication adherence is monitored with pill counts at each visit.

Concomitant non-psychotropic medications for stable conditions are allowed at the discretion of the study psychiatrist, who can also permit use of vitamins, supplements, oral contraceptives, and non-prescription analgesics. Patients on pre-existing stable doses are allowed to continue on zopiclone up to 7.5 mg prn or lorazepam 1–2 mg prn, to a maximum of 3 doses/week.

### Assessments

#### Clinical platform

The clinical assessments (Table 2) are selected based on theoretical and clinical utility and to minimize respondent burden as much as possible. Raters received training, and inter-rater reliability was established using recorded interviews. Clinician-rated symptom and clinical measures include the Montgomery-Asberg Depression Rating Scale (MADRS), using the structured interview guide (SIGMA) to enhance reliability [14, 15], and Clinical Global Impression, Severity and Improvement scales (CGI-S and CGI-I) [16]. Depressive and other associated symptoms are explored in greater detail using the Depression Inventory Development (DID) semi-structured interview, as part of the International Society for CNS Drug Development’s initiative to refine and validate a new measurement tool for use in clinical trials of MDD [17]. Patient-rated symptom scales include the Quick Inventory for Depressive Symptomatology (QIDS-SR) [18] and the Generalized Anxiety Disorder (GAD-7) scale [19]. Manic and hypomanic symptoms are assessed with the clinician-rated Young Mania Rating Scale (YMRS) [20] and the patient-rated Hypomania Check-List (HCL-32) [21].

**Table 2 Tab2:** Clinical characterization assessments

Clinician-Administered Assessments
Montgomery Asberg Depression Rating Scale (MADRS)
Young Mania Rating Scale (YMRS)
Clinical Global Impression (CGI)
Depression Inventory Development (DID) Interview
Toronto Side Effects Scale (TSES)
Sexual Side Effects Questionnaire (SexFX)
Childhood Experience of Care and Abuse (CECA)
Life Events and Difficulties Schedule (LEDS)
CNS Vital Signs (CNS-VS) computerized neuropsychological test battery
National Adult Reading Test (NART)
Self-Report Assessments
Quick Inventory of Depressive Symptomatology, Self-Report (QIDS-SR)
Generalized Anxiety Disorder 7-item scale (GAD-7)
Hypomania Check-List (HCL-32)
Brief Pain Inventory (BPI)
Sheehan Disability Scale (SDS)
Lam Employment Absence and Productivity Scale (LEAPS)
Quality of Life, Enjoyment and Satisfaction Questionnaire (Q-LES-Q)
World Health Organization Quality of Life Assessment (WHOQoL-BREF)
Pittsburgh Sleep Quality Index (PSQI)
Seasonal Pattern Assessment Questionnaire (SPAQ)
Biological Rhythm Interview of Assessment in Neuropsychiatry (BRIAN)
Dimensional Anhedonia Rating Scale (DARS)
Snaith-Hamilton Pleasure Scale (SHAPS)
Behavioural Inhibition/Behavioural Activation System (BIS/BAS)
NEO Five-Factor Inventory (NEO-FFI)
Experiences in Close Relationships (ECR-R) questionnaire
List of Threatening Experiences (LTE)
International Physical Activity Questionnaire (IPAQ)
Brief Diet Questionnaire

Self-rated scales are used to assess functional impairment (Sheehan Disability Scale; SDS) [22] and occupational functioning (Lam Employment Absence and Productivity Scale; LEAPS) [23]. Quality of life is measured both generally (World Health Organization Quality of Life Assessment; WHOQoL-BREF) [24] and with a specific focus on depression (Quality of Life, Enjoyment and Satisfaction Questionnaire; Q-LES-Q) [25], using these 2 self-rated measures.

We also assessed other behavioural and dimensional constructs, including aversive and incentive motivation (Behavioural Inhibition System/Behavioural Activation System; BIS/BAS) [26], anhedonia (Dimensional Anhedonia Rating Scale; DARS; and Snaith-Hamilton Pleasure Scale; SHAPS) [27, 28], personality (NEO Five-Factor Inventory; NEO-FFI) [29] and pain (Brief Pain Inventory; BPI-SF) [30]. Sleep, circadian rhythms, and seasonality are assessed using the Pittsburgh Sleep Quality Index (PSQI) [31], the Biological Rhythms Interview of Assessment in Neuropsychiatry (BRIAN) [32], and the Seasonal Pattern Assessment Questionnaire (SPAQ) [33]. Physical activity is measured using the self-rated International Physical Activity Questionnaire (IPAQ) [34], while dietary habits are assessed through a series of brief questions.

Assessment of environmental stressors includes adult patterns of attachment and recent stressful life events that are captured with self-report scales, including the Experience in Close Relationships (ECR-R) [35] scale, and the List of Threatening Experiences (LTE) [36], respectively.

Two clinical interviews are conducted by centralized, trained raters at Queen’s University and facilitated by Medeo, a secure telehealth/videohealth service (Medeo, Vancouver, BC, Canada). The Childhood Experience of Care and Abuse (CECA) [37], administered at Week 4 to patients and at Week 2 to healthy participants, is a semi-structured interview that carefully assesses childhood maltreatment. The Life Events and Difficulties Schedule (LEDS) [38], administered at Week 16 to all participants, is a semi-structured contextual interview and rating system that assesses stressful life events that have occurred within 6 months of depression onset. Interviews are audiotaped and transcribed so that responses can be coded based on standard, manualized conventions.

CNS Vital Signs (CNS VS) is a computerized test battery used to assess memory, reaction time and psychomotor speed, complex attention, and cognitive flexibility [39]. The reliability of CNS VS is similar to that of conventional neuropsychological tests [40]. The CNS VS has a robust normative database and is sensitive to common causes of cognitive impairment. Analyses of cognitive data will be augmented with an estimate of premorbid intelligence obtained using the National Adult Reading Test (NART) [41].

Medication side effects are documented with the clinician-rated Toronto Side Effects Scale (TSES) [42], which records the incidence, frequency, and severity of common adverse events, and the Sexual Functioning Questionnaire (SexFX), which evaluates specific sexual functioning [43]. Adverse Events are classified as mild, moderate or severe.

#### Neuroimaging platform

##### fMRI

Structural and functional neuroimaging data are obtained on 3.0 Tesla (3 T) magnetic resonance imaging (MRI) systems using multicoll phased-array head coils. Among the 6 clinical sites, 4 different models of scanners are used, thus mandating an extensive and ongoing standardization and quality control process to ensure that data are comparable and usable [44]. The four models of scanners include Discovery MR750 3.0T (GE Healthcare, Little Chalfont, Buckinghamshire, UK), Signa HDxt 3.0T (GE Healthcare, Little Chalfont, Buckinghamshire, UK), MAGNETOM TrioTim (Siemens Healthcare, Erlangen, Germany), and Achieva 3.0T (Philips Healthcare, Best, Netherlands). Cross-site T1 piloting included a “human phantom”, who travelled to each site for anatomical scans, and a manganese chloride (MnCl_2_)-based phantom model for progressive quantitative assessment of hydration based on signal intensity linearity characteristics [45]. Since the study’s launch, each site has obtained monthly scans of 2 geometric phantoms (a spherical agar phantom developed by the Function Bioinformatics Research Network, and a custom-built cylindrical model using plastic LEGO blocks) [46, 47] to facilitate scanner calibration and troubleshooting over the long term.

Following surveys and localization, the examination protocol includes a whole-brain T1-weighted turbo gradient echo sequence (9 min) at 1 mm^3^ resolution, repetition time (TR) = 6.2–1900 ms, echo time (TE) = 2.7–3.5 ms, flip angle = 8–15°, inversion time (TI) = 0–1100 ms, field of view (FOV) = 220–256 mm, matrix 256^2^–512^2^, 170–180 contiguous slices at 1 mm thickness. A small Vitamin E capsule is placed as a stereotactic marker at the right temple to confirm subject orientation during image review [48]. Secondly, a whole-brain diffusion tensor imaging (DTI) series is obtained using 30 gradient directions at 2 b-values (500 and 1000 s/mm^2^) (5 min) with an additional 3 images at b = 0 s/mm^2^ for tensor construction at a final voxel resolution of 2.3 x 2.3 x 5 mm (1 min). Functional MRI includes a 10-min resting state scan with eyes open using a fixation cross [49], obtained using a whole-brain T2*-sensitive blood oxygenation level-dependent (BOLD) echo planar imaging (EPI) series.

At the inception of the study, a BOLD EPI series was used during the Emotional Face Categorization/Conflict Task (2 runs of 7 min each) [50, 51]. After enrolling a cohort of 107 patients and 52 healthy participants, we substituted a reward paradigm and an implicit go no-go task. These tasks allow for the assessment of reward networks and attentional biases for affectively laden stimuli [52]. The substitution, rather than addition, of the functional tasks was necessary to maintain a feasible total time for participants in the scanner. The new tasks involve a 12-min hedonic function task [53, 54], where participants receive feedback and earn small monetary rewards while choosing correct responses among sets of visual stimuli and a 10-min affective go/no-go task to a series of stimuli that contain emotional content [55]. Stimulus sizes, instructions to participants, and support materials are standardized across sites. All behavioural data are captured using E-Prime software version 2.0 or higher (Psychology Software Tools, Sharpsburg, PA, USA).

##### Electroencephalography

The fMRI tasks were translated into analogous versions for electroencephalography (EEG), which is carried out at 4 sites, again using several equipment models (Biosemi ActiveTwo [BioSemi, Amsterdam, Netherlands], BrainVision Recorder/QuickAmp [Brain Products, Munich, Germany], Compumedics NeuroScan [Compumedics USA, Charlotte, NC, USA] , EGI Geodesic [Electrical Geodesics, Eugene, OR, USA]) that require cross-site consultation and standardization. All sites used a minimum of 64-channel caps and conductive electrode gels, with 53 common electrodes identified across the different systems. EEGs are digitized continuously (bandpass 0.04–100 Hz with 1000 Hz sampling rate) and all electrodes are referenced to the vertex (Cz) electrode.

At each session, participants complete a 10-min fixation resting state sequence with eyes open, followed by a 10-min resting state sequence with eyes closed. As with fMRI, the Emotional Face Categorization/Conflict Task was used for EEG when the study began, but was later changed to a task querying anhedonia in MDD and an affective go/no-go task, also using E-Prime software. Ocular artifacts, such as blinks, saccades, and lateral movements, are removed by independent component analysis (ICA) as implemented in EEGLAB [56] and performed using MATLAB (MathWorks, Natick, MA, USA).

#### Molecular platform

Blood and urine samples for genomic and proteomic analyses are collected from all participants at Weeks 0, 2, 8 and 16. Following blood draws at Weeks 0, 2, and 8, total RNA is immediately isolated from leukocytes and stabilized using the LeukoLOCK filter apparatus (Thermo Fisher Scientific, Waltham, MA, USA), which also depletes globin mRNA to improve the utility of samples for expression profiling and other applications. For patients with MDD, additional blood samples are collected at Week 4 for pharmacogenetic analysis and at Weeks 2, 10, and 16 for drug levels.

Standard Operating Procedures (SOPs) for sample receipt and accessioning, nucleic acid extraction, quality assessment, data tracking, DNA and RNA preparation for assays, scanning, and feature extraction are in place.

Objectives of the molecular platform are to investigate 1) candidate biomarkers for disease state or drug response in baseline samples in patients and healthy participants, 2) global DNA alterations that may correlate with disease state or drug response using baseline samples, and 3) dynamic molecules in pre- and post- treatment samples to identify pathways of drug response and select additional targets for investigation by targeted methods.

De-identified specimens are transferred to and stored at the Douglas Mental Health University Institute biorepository in accordance with regulatory guidelines and best practices for biobanking. A subset of samples is transferred to other CAN-BIND sites for specific analyses. Material transfer agreements between sites were established at the outset of the study.

Targeted analyses include DNA single-nucleotide polymorphism (SNP) open-array analysis to identify and sequence variants that correlate with disease state or drug response [57], along with studies using established methods for profiling of mRNA and miRNA sequences, histone modifications, and methylation status across the genome [58]. Proteomic analysis by selected-reaction monitoring mass spectrometry (SRM-MS) with state-of-the-art hybrid triple quadrupole/linear ion trap liquid-chromatography mass spectrometry (5500 and 4000 QTRAPs), will be used for relative quantification of high-interest plasma proteins within biological pathways with purported relationships to MDD [59].

Exploratory analyses include RNA-Seq for miRNA from blood and from plasma using either a HiSeq (Illumina, San Diego, CA, USA) or Proton (Thermo Fisher Scientific, Waltham, MA, USA) platform. DNA oxidative damage to guanine will be evaluated by measuring levels of 8-hydroxy-2-deoxyguanosine (8-OhdG) using a competitive ELISA analysis kit (StressMarq BioSciences, Victoria, BC, Canada). Cytosine oxidation will be measured using an ELISA-based assay to assess the levels of 5-hydroxymethylcytosine (MethylFlash™Methylated DNA Quantification Kit; Epigentek Group, Farmingdale, NY, USA). Global DNA methylation (i.e., 5-methylcytosine) will be evaluated using an ELISA-based method (Sigma-Aldrich, Darmstadt, Germany). Inflammatory markers in blood will be measured using standard antibody-based immunoassays.

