### Analyses

We will examine several outcomes, including responders at Week 8 who maintained response at Week 16, responders at Week 8 who are non-responders at Week 16, non-responders at Week 8 who respond at Week 16 with augmentation, and non-responders at Weeks 8 and 16, among other outcomes. A reasonably large dataset is required to study adequately the complex clinical, neuroimaging, and molecular factors that contribute to treatment outcomes. Our sample size target for this phase of the CAN-BIND program is 200 patients and 90 healthy participants (290 in total).

To identify standalone features that differ significantly between responders and non-responders, either at baseline or over the course of the study, parametric two-sample t-tests will be used for features with normally distributed data. Otherwise, the non-parametric Mann–Whitney *U* test will be used. A significance threshold of α = 0.05 and multiple testing corrections will be required. Given an input list of up to 25,000 features, of which at least 250 are differentially expressed between responders and non-responders, assuming an overall false discovery rate of 5 %, and applying two-sample t-testing procedures, a minimum of 49 subjects per category are required for power of at least 90 % to correctly identify a given feature which differs significantly between the categories. If nonparametric testing procedures are used, a minimum of 52 subjects per category are required to achieve the same power. Target recruitment for patients with MDD is 200. An estimated response rate of 60 % would yield 120 responders and 80 non-responders. The planned sample size is sufficiently powered for both parametric and non-parametric univariate testing. Multivariate analysis and the development of prognostic signatures of escitalopram response will follow univariate analysis.

Data analyses will be conducted using a suite of commercial and open-source software tools installed on high-end workstations at HPCVL. While data from each analytical platform will be independently analyzed using the methods described above, important relationships (either correlational or causal) between modalities can be detected through an integration of data collected across assessment platforms for a given study subject.

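### The two-sample tests named for platform features cannot adjust SNP-response comparisons for ancestry, although about 31% of the first patients are not White and ethnicity is already recorded

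*Protocol article*

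**What the plan says.** The Molecular platform section lists, among its targeted analyses, "DNA single-nucleotide polymorphism (SNP) open-array analysis to identify and sequence variants that correlate with disease state or drug response". It names no test for this work.

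The test comes from the Analyses section. The aim there is "To identify standalone features that differ significantly between responders and non-responders, either at baseline or over the course of the study", and for that aim "parametric two-sample t-tests will be used for features with normally distributed data". The alternative follows: "Otherwise, the non-parametric Mann–Whitney *U* test will be used". On error control the section says: "A significance threshold of α = 0.05 and multiple testing corrections will be required". It then extends the approach across platforms: "data from each analytical platform will be independently analyzed using the methods described above". No covariate, stratification factor or ancestry term appears.

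The information needed for adjustment is collected. Under Procedure, "Social background is collected using standardized reporting forms for demographic characteristics, handedness, ethnicity" are recorded at screening. Table 3 gives the ethnic make-up of the first cohort. Under Participants, healthy participants are matched on sex and age distribution only.

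**The concern.** An allele count takes the values 0, 1 or 2 and is not normally distributed. Read literally, the Analyses section therefore sends SNP features to the Mann–Whitney test, which compares two groups and has no place for a covariate.

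Allele frequencies vary by ancestry. If the chance of response also varies by ancestry, for whatever reason, then responders and non-responders differ in ancestry mix, and any SNP that tracks ancestry differs between them without any effect on drug response. A false discovery rate procedure takes the p-values as given. It controls error when the null p-values are valid, and for these SNPs they are not.

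In this study the univariate step comes before the multivariate analysis and the prognostic signatures, so an ancestry marker mistaken for a response variant could be carried into them.

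**Working it through.** **Inputs from the article.** Planned groups: 200 × 0.60 = 120 responders and 80 non-responders, as the article states. Ethnicity in Table 3: the counts add to 85 patients and 49 healthy participants. White patients are 59/85 = 69.4%, so 26/85 = 30.6% are not White. The largest single non-White category is Asian, 9/85 = 10.6%.

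**Assumptions not in the article.** Pooled allele frequency 0.3; allele-frequency gap *g* between the ancestry strata of 0.3 to 0.5; response rate lower by *D* = 0.10 to 0.20 in the minority stratum; minority share *q* = 0.11 (one group differs) or 0.31 (all non-White patients treated as one stratum).

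**Step 1: ancestry mix by response.** With 60% response overall, the minority response rate is r = 0.60 − (1 − q)D. The minority share is q·r/0.60 among responders and q(1 − r)/0.40 among non-responders.

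- q = 0.11: 9.4% v 13.4% at D = 0.10 (r = 0.511); 7.7% v 15.9% at D = 0.20 (r = 0.422).
- q = 0.31: 27.4% v 36.3% at D = 0.10 (r = 0.531); 23.9% v 41.7% at D = 0.20 (r = 0.462).

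**Step 2: first approximation.** The spurious allele-frequency difference is *g* times the difference in shares. Treating alleles as independent, SE = √[0.21 × (1/240 + 1/160)] = 0.047. The shift in z runs from 0.26 to 0.87 for q = 0.11 and from 0.57 to 1.91 for q = 0.31. The two-sided 5% test then rejects in about 6% to 14% and 9% to 48% of null SNPs.

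**Step 3: why this overstates the upper end.** A mixture of ancestries adds variance to the genotype. The variance of the allele count is 2p(1 − p) + 2q(1 − q)g². For q = 0.31 and g = 0.5 this is 0.42 + 0.107 = 0.527, so the SE grows by √(0.527/0.42) = 1.12. The shift falls from 1.91 to 1.70 and the rejection rate from 48% to about 40%.

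**Step 4: simulation of the named test.** Mann–Whitney with tie correction, 120 v 80, 40,000 null SNPs per setting, nominal 5%:

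| Minority share | D | g = 0.3 | g = 0.5 |
|---|---|---|---|
| 11% | 0.10 | 6% | 7% |
| 11% | 0.20 | 8% | 11–12% |
| 31% | 0.10 | 8% | 13% |
| 31% | 0.20 | 18–19% | 38–39% |

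Ranges reflect whether the exact share (9/85, 26/85) or the rounded one is used, and simulation error. With D = 0 the rate is 5% throughout. With ancestry in a linear model for allele count, it stays at about 5% in every setting.

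**Step 5: a stricter threshold does not cure it.** The power statement (25,000 features, 250 truly different, 5% FDR, 90% power) implies a per-test level of 0.05 × 250 × 0.9 / (0.95 × 24,750) = 0.00048. A separate simulation with a t-test, a 30.6% minority and allele frequencies of 0.20 v 0.50 gave rates of 0.002 at D = 0.10 and 0.0098 at D = 0.20, about 4 and 20 times that level. Using this threshold for SNPs is itself an assumption, because the article does not say that the 25,000-feature list describes the SNP array.

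**The case against.** The strongest reply is that this is a condensed article. It announces a master Statistical Analysis Plan, to which expert working groups contribute, and ancestry terms in genotype tests are commonly specified there. The word unadjusted does not appear, and the power statement speaks of features that are "differentially expressed", which suggests gene expression rather than SNPs. This stands in part: the plan may already contain the adjustment. But the article does more than stay silent. It names the tests and extends them to each platform, and the tests it names cannot be adjusted. A plan that followed it would inherit the problem, and one that did not would depart from it.

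A second reply is that no response rate by ethnicity is given, so the 10 to 20 point differences are illustrative. That stands in full. Treating Arab, Asian, Black, Latin American, Other and Mixed participants as one genetic stratum is also unrealistic, which is why the 31% figures are an upper range. The 31% itself describes the first 85 patients, not the planned 200.

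A reader might also infer that the comparison of patients with healthy participants is confounded, since SNPs are sought for disease state too and matching ignores ethnicity. The article does not support that. Its named tests are for responders against non-responders, and it names none for SNPs by disease state. The non-White shares are close: 26/85 = 30.6% v 14/49 = 28.6% (Fisher p = 0.85; all categories p = 0.63). At 200 v 90 with those shares and the same allele gaps, the simulated Mann–Whitney error rate is about 5%. The Asian share alone differs more (9/85 = 10.6% v 9/49 = 18.4%), but with p = 0.29 this is compatible with chance. Broad categories and small numbers do not exclude finer confounding; they do not show it either.

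Finally, the Conclusion presents the findings as hypotheses for later validation. This lowers the stakes but does not make the named test suitable.

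**Conclusion.** The point holds for SNPs and drug response. The tests named in Analyses, applied to each platform as the article says, cannot account for ancestry in a cohort where about three in ten patients are not White, and multiple-testing correction does not repair this. The true size cannot be derived from the article: it is nil if response does not vary by ancestry, about 6% to 11% at the nominal 5% level if one 11% group differs, and about 8% to 39% at the upper range, all under the assumed response differences and allele-frequency gaps. The article does not show that confounding has occurred, and no claim is made about disease state. It is a worthwhile correction to a stated method, not a flaw that undermines the study.

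**What to change.** In Analyses, exempt SNP features from the two-sample tests. For example: for SNP features, response will be analysed by logistic regression on allele count with ancestry in the model, using genetic principal components where the array carries enough markers and otherwise the self-reported ethnic group recorded at screening; a test stratified by ethnic group is an acceptable equivalent. If the master Statistical Analysis Plan already specifies this, a cross-reference that overrides the general sentence is enough. If SNPs are also compared between patients and healthy participants, use the same ancestry-adjusted model.

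The change is to the analysis wording and uses data already planned. It costs a few degrees of freedom and slightly lower power for SNPs that are correlated with ancestry. Sparse ethnic categories (Table 3 has one Black and three Arab patients) would need a grouping rule set before the analysis if self-report is used. The sample size does not change.
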